# 2.2 Recruitment Criteria

One to two weeks after the monthly training, trainees from the latest cohort who have completed the course will be recruited for our study on a voluntary basis. Additionally, any physician who has undergone relevant training (ultrasound-guided CVC insertion) and is willing to participate will be included.

# 2.3 Recruitment Methods

Posters will be placed in the Clinical Skills Center (Simulation Medical Education Center). Those who attend the regular courses will receive detailed information. E-mails will be sent to participants of the regular courses inviting them to join the research program, and announcements will be made on educational community websites.

# 2.4 Recruitment Numbers and Sample Size

A power calculation cannot be executed for this research due to the absence of extant data on the application of AR-US in CVC placement. This deficiency precludes the computation of the standard deviation for the primary outcome measure.

- Anticipated enrollment in Linkou CGMH (L): 50.
- Anticipated enrollment in Keelung CGMH (K): 50.

# 2.5 Trial Procedures, Randomization

After a verbal explanation from the principal investigator and the project staff, participants will be enrolled in the study. Each participant in the district will be assigned a number, ranging from L 1-50 for Linkou and K 1-50 for Keelung.

Prior to entering the trial, participants will fill out a questionnaire, then undergo a pre-test. After the pre-test, they will proceed to the main trial.

For each trial, participants will be randomly assigned (by coin-toss) into one of two groups. Group A will first perform the ultrasound-guided CVC insertion using AR smart glasses to display the US images (AR-US). After completing the task, they will rest for 10 minutes and then perform the ultrasound-guided CVC insertion using a standard US monitor (S-US) without AR glasses. Group B will first perform the ultrasound-guided CVC insertion using S-US, without AR glasses. They will then rest for 10 minutes, and then perform the insertion using AR-US. Each participant must complete the following steps during the CVC insertion activity:

1. Identify anatomy of the insertion site and localization of the vein.
2. Confirm patency of the vein. (Target vessel: right internal jugular vein)
3. Use real-time US guidance for puncture of the vein.
4. Confirm needle position in the vein.
5. Confirm wire position in the vein.
6. Confirm catheter position in the vein.

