**Synopsis**

Augmented reality (AR) was initially developed for military purposes and later expanded to everyday life. Currently, AR has found its way into both medical and educational applications.

Central venous catheterization is a vital procedure for managing critically ill patients. Research has confirmed that using real-time ultrasound guidance during the puncture and catheter insertion process substantially enhances its efficacy and safety profile. However, in the standard approach, the use of ultrasound imaging requires that physicians frequently switch focus between the ultrasound monitor and the procedural site. This constant shifting of visual and mental focus intensifies the cognitive burden on the medical professional, leading to "task interruptions and task-switching." Novice physicians attempting to master the CVC procedure may find that this act of task-switching and the ensuing interruptions poses additional, unnecessary challenges, a serious issue that demands greater attention in medical education.

Taking the placement of a central venous catheter as an example, we can now leverage technology to integrate the ultrasound view with the surgical view through the use of AR smart glasses. The ultrasound images are transmitted to the glasses, which also allow a view of the procedure site at the same time, thus reducing the frequent task-switching and its associated cognitive burden. This innovative approach is anticipated to minimize interruptions and transitions during invasive surgeries. We hypothesize that by reducing the cognitive load on the operator, the efficacy of invasive procedures can be enhanced, leading to increased success rates and improved patient safety.

We will conduct a prospective randomized crossover trial to investigate the performance and cognitive load of physicians performing ultrasound-guided central venous catheter (CVC) placement using ultrasound imaging displayed on an AR-enabled head-mounted display (AR-US). The participants will be divided into two groups of 50 each and will take part in a crossover trial involving ultrasound imaging using a traditional monitor and ultrasound imaging using AR glasses. The primary and secondary outcomes will be (1) the number of successful/unsuccessful punctures, (2) the total time taken, and (3) self-assessment of cognitive load. The results of this research as anticipated could be broadly applied to any invasive procedure requiring ultrasound guidance.

Table of Contents

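### Sequence is assigned by an unrestricted coin toss, which would rarely give two sequences of 50 if that is what the Synopsis means, and no safeguard against a repeated or overridden toss is described

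*Protocol*

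**What the plan says.** The Synopsis states that "The participants will be divided into two groups of 50 each and will take part in a crossover trial" comparing the two displays. Section 2.4 uses the same number for the hospitals: "Anticipated enrollment in Linkou CGMH (L): 50" and "Anticipated enrollment in Keelung CGMH (K): 50". Section 2.5 numbers participants accordingly, "ranging from L 1-50 for Linkou and K 1-50 for Keelung".

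Section 2.5 then uses the word groups for the sequences. Group A works with the AR glasses first and the standard monitor second; Group B does the reverse, with ten minutes' rest between tasks. The method is that "participants will be randomly assigned (by coin-toss) into one of two groups". No sequence sizes, blocking or stratification by hospital are given, and the section does not say who tosses or how the result is recorded.

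The toss is described after enrolment, the questionnaire and the pre-test: "After the pre-test, they will proceed to the main trial". By section 3.1.1 the questionnaire covers rank and past experience with CVC insertion, with and without ultrasound. By section 3.1.2 the pre-test measures knowledge of the procedure. The Data Analysis section plans a 2 x 2 ANOVA with method as the within-participant factor and sequence as the between-participant factor.

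**The concern.** There are two separate issues.

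The first is balance. Independent tosses fix neither the overall split between sequences nor the split within a hospital. If the Synopsis is promising 50 participants per sequence, the stated method will usually miss that figure. Each participant does the same six-step task twice, so a practice effect is plausible, although the protocol does not quantify it. Unequal sequences let part of such an effect into any unadjusted comparison of AR-US with S-US.

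The second is integrity. By the time of the toss, likely predictors of performance may already be known to those present. A toss can be repeated or set aside without trace unless something is in place to prevent it, and the protocol describes nothing of the kind. If order came to depend on ability, the between-sequence comparison would no longer be a randomized one. Under the condition derived in the working, the method contrast would be affected too.

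**Working it through.** **The plan's own figures.** Section 2.4 gives 50 + 50 = 100, and the Synopsis gives 2 x 50 = 100. The totals agree. There is no power-based sample size to reproduce, because section 2.4 states that "A power calculation cannot be executed for this research due to the absence of extant data".

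**Assumptions.** The coin is fair, with one independent toss per participant and 100 participants, 50 at each hospital. Section 2.5 is not explicit about the unit of the toss; one per participant is the likely reading.

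**Split over the whole trial.** The size of Group A is Binomial(100, 0.5).
- P(exactly 50:50) = C(100,50)/2^100 = 0.0796, so an unequal split has probability 1 - 0.0796 = 0.920.
- P(55:45 or worse) = 2 x P(X <= 45) = 0.368.
- P(60:40 or worse) = 2 x P(X <= 40) = 0.0569.

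**Split within hospitals.** Each hospital is Binomial(50, 0.5).
- P(25:25 at one hospital) = C(50,25)/2^50 = 0.1123. At both: 0.1123^2 = 0.0126.
- P(30:20 or worse at one hospital) = 0.2026. At one hospital or more: 1 - (1 - 0.2026)^2 = 0.364.

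**Precision.** For the period-adjusted method contrast in a 2 x 2 crossover, efficiency relative to equal sequences is 4 nA nB / N^2.
- 55:45: 4 x 55 x 45 / 10,000 = 0.99; SE factor 1/sqrt(0.99) = 1.005.
- 60:40: 4 x 60 x 40 / 10,000 = 0.96; SE factor 1/sqrt(0.96) = 1.021.
- Averaged over all possible tosses, expected efficiency is 0.99.

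**Raw method means.** Let p be the change from Phase 1 to Phase 2 due to practice. The AR-US mean contains (nB/N)p and the S-US mean contains (nA/N)p. The raw difference between methods therefore shifts by |nA - nB|/N of p: (60 - 40)/100 = 20% at 60:40, and (55 - 45)/100 = 10% at 55:45. At 50:50 the shift is zero.

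**Adjusted method contrast.** Let t be the method effect (AR-US minus S-US), and let pA and pB be the mean practice gains in the two sequences. The within-person difference averages t - pA in Group A and t + pB in Group B. Giving the sequences equal weight yields t + (pB - pA)/2. If assignment is truly random, pA and pB are equal in expectation and the practice effect cancels whatever the split. If order is steered by ability and practice gain depends on ability, pA and pB differ and a bias of (pB - pA)/2 remains. The documents give no figures from which to size it.

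**The case against.** The strongest reply is that little of this threatens the primary result. Everyone performs both methods, so differences in overall ability cancel within person. Sequence is in the ANOVA, equal sequence sizes are not required, and the loss of precision is trivial. All of that stands. The low probability of an exact 50:50 split measures departure from a stated figure, not loss of validity.

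It can also be said that the groups in the Synopsis may be the hospitals, in which case the toss contradicts no stated number. That reading is possible. The sentence goes on directly to the crossover, however, and section 2.5 uses groups for the sequences, so the sequence reading is the more natural. On the hospital reading the protocol gives no sequence size at all.

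A reader might infer two stronger criticisms, neither of which the documents support:
- That the toss fails to conceal the next assignment. A fair independent toss can be guessed with probability only 0.5, and it is described after enrolment. Fixed blocks without concealment would be more predictable.
- That the plan confuses hospitals with sequences. Fifty per hospital and fifty per sequence are compatible, for example with 25 per sequence at each hospital. The text leaves the meaning unclear; it does not show an error.

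Finally, silence about who tosses and how it is recorded does not prove that no record would be kept, and nothing suggests that tosses would be repeated. The point is only that no safeguard is described.

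**Conclusion.** The point holds in a limited form. If the Synopsis means two sequences of 50, the stated method delivers that only 8.0% of the time, and it gives 25:25 at both hospitals 1.3% of the time. These figures assume a fair coin, one toss per participant and full enrolment of 100.

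The statistical cost of chance imbalance is small: about 2% on the standard error at 60:40, with the planned method contrast protected by the sequence factor provided the sequences are weighted equally. Only unadjusted method means take up part of a practice effect.

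The more useful reason to change is that the protocol describes nothing to stop a toss being repeated or overridden after ability-related information is in hand. Steering would distort the sequence effect, and would bias the method contrast only if practice gains also differ by ability. Neither is shown to be likely. This is an inexpensive improvement worth making, not a flaw that invalidates the design.

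**What to change.** In section 2.5, replace the coin toss with a computer-generated list prepared before enrolment by someone not enrolling participants. Use permuted blocks stratified by hospital, with varied block sizes that sum to 50 per hospital; five blocks of 4 and five of 6 in random order would do (20 + 30 = 50). Each block is split equally, giving 25 per sequence at each hospital and 50 per sequence overall at full enrolment. Tie the list to L 1-50 and K 1-50, conceal it from those enrolling (sealed opaque envelopes or a locked file), and open each assignment only after that participant's pre-test. State who holds the list and who opens each assignment.

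Reconcile the Synopsis, section 2.4 and section 2.5 so that all three say 100 participants, 50 per hospital, 25 per sequence within each hospital. Keep the word group for the sequences only.

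The cost is slight preparation work and a wording change, with no extra participants. The trade-off is that blocks, unlike tosses, can become guessable near the end of a block, so the block sizes must stay varied and undisclosed. Adding hospital to the analysis model is optional.

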# 2.6 Trial Flowchart

1. Trainees enrolled.
2. Completion of trainees’ basic information questionnaire.
3. Written pre-test, ten multiple-choice questions.

S-US guided CVC

10 Mins rest

S-US guided CVC

NASA Task Load Index

NASA Task Load Index

AR-US guided CVC

10 Mins rest

AR-US guided CVC

NASA Task Load Index

NASA Task Load Index

Analysis

Randomly assigned.

**Before study entry**

**Phase 1**

**Phase 2**

Figure 7. Study flowchart. * The parameters collected include the following: First pass rate, number of attempts, venous access time (seconds), catheterization time (seconds), artery puncture times, total time, success/failure rates, lag time (ultrasound to venous access time), and the number and duration of operator head turns. .

# Preferred Trial Timetable

Preferred Start Date: 1st August 2021

Expected Date of Completion: 31st July 2022

# 2.8 Task Simulator

CAE Gen II Ultrasound Central Line Training Model, Opaque Insert. (Figure 8)

[figure not shown]

Figure 8. CAE Gen II Ultrasound Central Line Training Model

# 2.9 Smart Glasses

Foresee-X Smart Surgical Glasses produced by Taiwan Main Orthopedic Biotechnology Company (Figure 9)

[figure not shown]

Figure 9. Foresee-X Smart Surgical Glasses.

# Data Collection

3.1 Plans for Assessment and Collection of Outcomes

# 3.1.1 Characteristics of participants

Collect participant information (questionnaire): Data collected includes name, gender, position/rank, dates of course attendance, past experience with CVC insertion, and past experience with ultrasound-guided CVC insertion.

# 3.1.2 Pre-test

Preliminary assessment of participants: Ten questions, derived from past National Physician Examination questions, will be used primarily to test the participants' knowledge about central venous catheter placement but also as a reference for scoring intrinsic load (IL).

# 3.1.3 Primary Outcomes: Performance of CVC Placement

Parameters to be assessed during the CVC placement process include: first pass rate, number of attempts, venous access time (in seconds), catheterization time (in seconds), number of artery punctures, total time, success/failure rate, lag time (from ultrasound to venous access), and the number and duration of operator head turns. There are two methods for collecting these parameters. The first is through continuous recording to collect data on the time spent by the operator, number of punctures, head movement durations, etc. The other method uses the WOMBAT - Work Observation Method by Activity Timing software, developed by Macquarie University.

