# 3.1.4 Secondary outcomes: Cognitive load Evaluation

Cognitive Load Questionnaire Collection: This includes intrinsic load (IL), extraneous load (EL), and germane load (GL) experienced during the experiment. Three scales are used for assessment: the Paas cognitive load scale, the NASA Task Load Index, and the Rating Scale Mental Effort (RSME). All three scales are employed to evaluate the participant's IL, EL and GL."

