# Data Analysis

The research data will be processed using IBM® SPSS® Statistics v26. The data will be presented as mean values and standard deviations (for continuous variables) or counts and percentages (for categorical variables). The primary analysis will employ a 2 x 2 ANOVA (within: intervention method, between: sequence) to statistically compare the continuous variables – specifically: success rate, placement time, and cognitive load. If the sphericity assumption is violated, the Greenhouse-Geisser estimate will be used to adjust the degrees of freedom. All effects will be considered significant at p < .05.

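### The protocol contradicts itself on which outcomes are primary and declares every effect significant at an unadjusted .05

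*Protocol*

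**What the plan says.** Four places in the protocol bear on what is primary.

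- **Synopsis.** "The primary and secondary outcomes will be (1) the number of successful/unsuccessful punctures, (2) the total time taken, and (3) self-assessment of cognitive load". The sentence covers both classes of outcome at once and does not assign the items to them.
- **Section 3.1.3**, headed "3.1.3 Primary Outcomes: Performance of CVC Placement". The parameters assessed during the placement "process include: first pass rate, number of attempts, venous access time (in seconds), catheterization time (in seconds), number of artery punctures, total time" and then "success/failure rate, lag time (from ultrasound to venous access), and the number and duration of operator head turns". That is six measures plus four, or nine in total if number and duration of head turns count as one. None is singled out. The note to Figure 7 repeats the list, also unranked.
- **Section 3.1.4**, headed "3.1.4 Secondary outcomes: Cognitive load Evaluation". Cognitive load is secondary and is measured on three scales: Paas, NASA Task Load Index and RSME.
- **Section 4, Data Analysis.** The primary analysis is a 2 x 2 ANOVA (method within, sequence between) of three variables, "specifically: success rate, placement time, and cognitive load". The section adds: "All effects will be considered significant at p < .05".

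No section gives a hierarchy, a multiplicity adjustment or a rule for calling the trial positive. Section 2.4 says that no power calculation was possible, so the sample size does not show which outcome was meant either.

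**The concern.** Sections 3.1.3, 3.1.4 and 4 cannot all be followed. A measure that is secondary in 3.1.4 sits inside the primary analysis of Section 4. Most of the measures that are primary in 3.1.3 are not named there. The placement time of Section 4 does not appear under that name in the 3.1.3 list. The success variable is also open: 3.1.3 offers first pass rate, number of attempts and success/failure rate, the Synopsis counts successful and unsuccessful punctures, and Section 4 speaks of a success rate.

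With a flat .05 for every effect, the text does not prevent a result on one of several measures, picked after the data are seen, from being reported as the primary finding. Section 1.3 looks to this study as validation for wider use of the glasses in other ultrasound-guided procedures, so a selectively supported claim would have consequences. At stake are a defined primary question and a controlled type I error for it.

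**Working it through.** The protocol states no familywise error to reproduce. Its only figure is the .05 per effect in Section 4.

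**Inputs**
- Level per test: .05 (Section 4). The method effect has one degree of freedom, so its F test is equivalent to a two-sided test.
- Number of tests m: 3 (Section 4), or 10 (Section 3.1.3), or 9 if head turns are one item.
- Correlation between test statistics: not given. Assumed equal for all pairs, at 0, 0.3, 0.5, 0.7 and 0.9.
- Rule for a positive result: not given. Assumed here that any one significant method effect suffices.

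**Independent tests:** familywise error = 1 - (1 - 0.05)^m
- m = 3: 1 - 0.95^3 = 14.3%
- m = 9: 1 - 0.95^9 = 37.0%
- m = 10: 1 - 0.95^10 = 40.1%

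**Correlated tests:** simulation of equicorrelated two-sided normal tests, 400,000 draws

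| Correlation | m = 3 | m = 10 |
|---|---|---|
| 0 | 14.2% | 40.1% |
| 0.3 | 13.6% | 35.2% |
| 0.5 | 12.5% | 28.6% |
| 0.7 | 10.9% | 21.3% |
| 0.9 | 8.3% | 12.8% |

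For two-sided, jointly normal statistics the Sidak inequality makes the independence value the maximum, so 40.1% is a ceiling for ten tests. The table counts one method effect per measure. Using each cognitive-load scale separately, or counting the sequence and interaction effects, would add tests.

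**After the fix:** one primary outcome at .05 gives 5%. A fixed order at .05, or Holm over three outcomes, holds the familywise error at 5% or less.

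**Price of Holm:** N = 50 + 50 = 100 (Section 2.4), paired comparison, 80% power assumed, effect in SDs of the within-person difference.
- At .05: (1.960 + 0.842)/sqrt(100) = 0.280; with the t distribution, 0.283.
- At the strictest Holm step, .05/3 = .0167: (2.394 + 0.842)/sqrt(100) = 0.324; with the t distribution, 0.328.

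The detectable effect therefore rises from about 0.28 to about 0.33 SD.

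**The case against.** A reader might infer several stronger things that the text does not carry.

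- **A 40% chance of a false primary claim.** This needs ten independent tests and a rule that any one of them suffices. No section states that rule. Section 3.1.3 sits under Data Collection and lists parameters to be assessed, while the section that fixes tests names three variables. Independence is also implausible: number of attempts determines first pass, the access, catheterization and total times appear to overlap, and head-turn number and duration go together. The objection stands, so 40% is only a ceiling.
- **Three different outcome sets.** The Synopsis, Section 1.3 and Section 4 give broadly the same triad of success, time and cognitive load. The conflict is between that triad and the longer list in 3.1.3, plus the label on cognitive load.
- **Any of four times could serve as placement time.** Venous access time and lag time end at venous access, before a catheter is placed. Only catheterization time and total time are plausible, and the Synopsis points to total time.

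Two further defences carry less weight. The primary analysis in Section 4 may mean only the main statistical method. That would remove the apparent promotion of cognitive load but would leave the primary measures unranked. A statistical analysis plan that is not shown may set a hierarchy, and this is a simulator study that speaks of feasibility. That tempers the consequence. Still, no such plan can implement the Synopsis, 3.1.3, 3.1.4 and Section 4 together as they stand.

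**Conclusion.** The point holds as an internal contradiction about what is primary, joined to an unadjusted .05 for every effect. It does not rest on detail that a protocol may leave to an analysis plan.

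Its size depends on which list governs, and the protocol does not settle that. If any one significant result is taken as a positive primary finding, the familywise error is about 11-14% on Section 4's three variables (each tested once, correlation 0.7 to 0). It is about 13-35% if all ten measures are tested (correlation 0.9 to 0.3), and at most 40% under independence. The correlations and the any-one rule are assumptions. Even the lower range is at least twice the nominal 5%.

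**What to change.** Before the data are analysed:

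1. Name one primary outcome in identical words in the Synopsis, Section 3.1.3 and Section 4.
2. If it is a time, use total time with start and end points defined by the sponsor, put it in place of the term placement time, and state how failed placements are counted. The protocol gives no simulator success rate, so few failures cannot be presumed.
3. Test the other two outcomes of the triad, one success measure and one prespecified cognitive-load score, in fixed order at two-sided .05. Alternatively, use Holm over the three.
4. Report all other parameters as exploratory, with confidence intervals and no significance claim. Limit the .05 statement in Section 4 accordingly.

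The cost is wording only; no new participants or data are needed. The downside is that the other measures lose confirmatory status. With Holm there is also the modest loss of sensitivity worked out above, at the strictest step.

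### Placement time is fixed as an ANOVA on raw means, but the protocol defines neither a failed insertion, nor an observation limit, nor the time a failure receives

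*Protocol*

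**What the plan says.** Section 3.1.3 of the protocol names as primary outcomes the first pass rate, number of attempts, venous access time, "catheterization time (in seconds), number of artery punctures, total time, success/failure rate", lag time and head turns. The footnote to the study flowchart (Figure 7) repeats the list.

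The Data Analysis section states: "The primary analysis will employ a 2 x 2 ANOVA (within: intervention method, between: sequence"). It applies this "to statistically compare the continuous variables – specifically: success rate, placement time, and cognitive load". The summaries are also on the raw scale: "The data will be presented as mean values and standard deviations (for continuous variables"). The threshold is "All effects will be considered significant at p < .05". No transformation, censoring or rank method is named. The section does not say which of the listed times is meant by placement time.

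Two other places bear on whether an insertion can fail. Section 2.5 says "Each participant must complete the following steps during the CVC insertion activity" and lists six steps, ending with the catheter position. The Synopsis counts successful and unsuccessful punctures, not insertions. Neither gives a time limit, an attempt limit or a rule for abandoning the task.

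**The concern.** A within-participant ANOVA needs a number from each participant under both displays. An insertion that never reaches the vein has no venous access time, and one that stops at the wire has no catheterization time. Because success or failure is itself an outcome, the plan allows for such insertions, yet its chosen method has no place for an unfinished time.

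Two things can then happen. If the time is left blank, a repeated-measures ANOVA as usually run uses complete pairs only, so a failure with one display also removes that participant's result with the other. If the time until giving up is entered, a quick failure counts as a fast insertion. Failures are likely to be the slow or difficult insertions, so both routes tend to hide a real time difference.

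When observation ends is also a rule of trial conduct. It has to be in force, identically in both phases, before the first participant starts. An analysis plan written later cannot supply it.

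**Working it through.** **No figure of the plan can be reproduced.** Section 2.4 says "A power calculation cannot be executed for this research due to the absence of extant data on the application of AR-US in CVC placement", and no SD, effect size or failure rate appears anywhere. The planned number is 100: "Anticipated enrollment in Linkou CGMH (L): 50", and the same at Keelung. Everything below rests on assumed values.

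**Step 1: pairs lost.** If failed insertions have no time and failures are independent between displays, participants retained = 100 × (1 − pS) × (1 − pA), where pS and pA are the failure rates on S-US and AR-US.
- No failures: 100
- 5% and 5%: 100 × 0.95 × 0.95 = 90.2
- 10% and 5%: 100 × 0.90 × 0.95 = 85.5
- 20% and 10%: 100 × 0.80 × 0.90 = 72.0
- 30% and 30%: 100 × 0.70 × 0.70 = 49.0

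**Step 2: main illustration.** Assumed: log-normal times, S-US median 180 s, log-SD 0.7, within-person correlation 0.5, AR-US time ratio 0.8 (median 144 s), and failure if not finished by 480 s.
- Mean times: 180 × exp(0.7²/2) = 230 s and 144 × exp(0.7²/2) = 184 s. The true difference is −46 s.
- Failures: 1 − Φ(ln(480/180)/0.7) = 1 − Φ(1.40) = 8.1% on S-US; 1 − Φ(ln(480/144)/0.7) = 1 − Φ(1.72) = 4.3% on AR-US.

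Trials of 100 participants were simulated several thousand times. A paired t-test stood in for the within-participant F test, with no period effect. Give-up times were assumed uniform from 60 to 240 s. Powers vary by about one point between runs.

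| Handling of failures | Mean difference | Power |
|---|---|---|
| All true times known, raw | −46 s | 75% |
| Pairs with a failure dropped (11% lost), raw | −31 s | 74% |
| Give-up time entered, raw | −24 s | 54% |
| Failures kept at the limit, raw | −37 s | 84% |
| Failures kept at the limit, log scale | ratio | 88% |

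The shrinkage is (46 − 31)/46 = 33% with pairs dropped and (46 − 24)/46 = 48% with give-up times. Keeping failures at the limit also shrinks the raw mean, by (46 − 37)/46 = 20%. Its advantage is that nobody is removed and power is higher. It does not recover the uncensored mean.

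**Step 3: more failures.** With an S-US median of 240 s and the rest unchanged, 21% of pairs are lost. Power is 66% with pairs dropped and 85% with failures at the limit, both raw. Entering give-up times gives about −19 s and 31% power.

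**Step 4: other assumptions.** With S-US median 120 s, log-SD 0.5 and ratio 0.8, the true difference is about −27 s and power with all true times is about 0.98.

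| Failures S-US / AR-US | Pairs kept | Difference, pairs dropped | Power, pairs dropped |
|---|---|---|---|
| 5% / 2% | 94 | −22 s | 0.97 |
| 10% / 4% | 87 | −19 s | 0.96 |
| 20% / 10% | 75 | −16 s | 0.91 |
| 30% / 17% | 63 | −14 s | 0.82 |

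**Step 5: no true effect.** With equal displays, the type I error stays at about 5 to 6%. With a true effect and pairs dropped in the Step 2 scenario, the estimate keeps the correct sign in over 99% of trials.

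**The case against.** The strongest reply is that few or no whole insertions may fail. Section 2.5 requires all six steps to be completed, the participants have been trained, the task is on a simulator with no stated time limit, and the Synopsis speaks of punctures. Failure might then mean a missed puncture within an insertion that is later completed and has a time. This stands as a limit on size. It does not settle the matter: success/failure is listed separately from number of attempts and first pass rate, which already capture missed punctures. The uncertainty about the unit is itself a reason to define it.

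A second reply is that missing-data rules usually belong in the SAP, which is not shown. That is fair for missing-data detail. It does not cover the choice of primary method, which the protocol has made, or the end of observation, which must be set before the trial runs.

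A reader might infer three stronger things that the documents do not support:
- **That the time comparison will be made in a subset selected by outcome.** No section excludes failed insertions, and total time could be recorded up to abandonment.
- **That the time effect could point the opposite way from the success effect, or that false positives would rise.** The simulations show neither. That the dropped participants are those whom AR-US helped most is likewise an assumption.
- **That dropping failures costs 14 power points (74% against 88%).** That contrast changes both the handling of failures and the scale. On the raw scale it is 74% against 84%, and against fully known raw times dropping costs only about 1 point in Step 2.

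Raw-scale ANOVA on right-skewed times is not an error in itself. With about 100 pairs it holds its size, and what is lost is efficiency.

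**Conclusion.** The concern holds in conditional form. The protocol commits placement time to a method that cannot take an unfinished time, while expecting success or failure as an outcome and fixing neither a definition of failure, nor a limit, nor a time for failures. If insertions fail, following the text leads to a comparison among double successes or to a mixture of give-up and completion times.

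The harm shown is an attenuated difference and lower power than a method that keeps failures. In the main illustration that is 33% or 48% attenuation, and raw-scale power of 74% or 54% against 84%. These figures rest on an assumed median, spread, correlation, limit and give-up time, and on failure meaning slowness. With failures of 5% and 2% the power loss is about one point, although the difference still shrinks from −27 to −22 s. With no failed insertions there is no loss from this source. This should be fixed before the trial starts; it is not fatal to it.

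**What to change.** 1. Define failure of an insertion as distinct from a failed puncture, and bring the Synopsis, section 2.5 and section 3.1.3 into agreement on it. State which recorded time is placement time.
2. Set one observation limit for the simulator task, the same in both phases. The investigators should choose it; the 480 s above is only an illustration.
3. Keep every participant in the time analysis, with failures censored at, or ranked worse than, that limit. Use a period-adjusted rank-based crossover test (Koch), or a Cox model stratified by participant with period as covariate. The Cox version uses only which of a participant's two times is shorter, so it may be the less efficient choice. The powers above are for paired t-tests and should not be carried over to either method.
4. Report the AR-US/S-US ratio of geometric mean times as supportive, and success-only times descriptively.

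The cost is analysis wording and one operational limit, since the continuous recording in section 3.1.3 already captures the times. The downside is that the effect is stated as a ratio or rank effect instead of a raw difference in seconds.
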